### Statistical analysis plan

All quantitative data will be entered into a purpose-designed database and exported for statistical analysis in relevant statistical software. Members of the research team, including a statistician, will conduct the analysis. The analyses that will be performed will include:The extent of sarcopenia in the three target chronic inflammatory diseases using several methods to assess muscle mass, function and strength and compare these data with the EWGSOP criteria.Identification of potential mechanisms of sarcopenia that occur in CLD, IBD and RA achieved through a multi-modal assessment process.Assessment of any longitudinal changes in each cohort over a 6-month period following their standard of care.Assessment of the best non-invasive assessment parameters for evaluation of sarcopenia will be made via analysis of the results of anthropometric, functional, and imaging data, using non-parametric analysis via Spearman correlation. Specifically, we will carry out the following:Baseline descriptions of clinical parameters and sarcopenia with proportions demonstrated and median and mean formulated.Correlation analysis of measures of sarcopenia and how they relate to disease severity, QoL, etc., will be performed by qualitative measures.Comparisons between disease types will be made using non-paired, non-parametric testing.Dynamic changes over 6-months (pre and post 6-months of standard of care treatment) will be assessed using paired, parametric and non-parametric testing.

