### Study design

#### Patient selection and sample

A target of fifty patients (over the age of 18 years) will be selected from:Patients with CLD, predominantly liver cirrhosis or end-stage liver disease (ESLD)) who are being assessed for liver transplantation (LT). A further twenty patients with non-alcoholic related fatty liver disease (NAFLD), confirmed by transient elastography +/− liver biopsy, with significant fibrosis (Kleiner fibrosis stages F2–F4) and without ESLD will also be identified and recruited for comparison.Patients with active IBD who are undergoing medical management only and are due to commence a new biologic treatment.Patients with active rheumatoid arthritis (RA) who are commencing a new biologic treatment.

We will also recruit an age-sex matched sample of twenty healthy individuals as a control cohort for comparison.

This is an observational prospective cohort study with deep phenotyping (experimental) of each patient group to determine the mechanisms underlying sarcopenia in each cohort, therefore a sample size calculation was not applicable. However, we calculated that 50 patients per disease group is sufficient for a Spearman correlation of ≥0.3 to reach statistical significance. Recruitment targets are also based on feasibility within the time frame of the study and based on the planned statistical analysis, described below.

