#### Experimental variables

The primary experimental variables for this study are:To identify the best non-invasive assessment parameters to evaluate sarcopenia in CLD, IBD and RA and acquire data for the degree of sarcopenia in each disease cohort (muscle area, strength, functional state and activity indices).To identify any longitudinal change in measures as determined by change in muscle mass, strength and function over a 6-month period, in concordance with their clinical status and treatment.

The disease-specific secondary experimental variables related to mechanisms potentially driving sarcopenia are highlighted in Table 2.

**Table 2 Tab2:** Secondary outcome measures

CLD	IBD	RA
• Change in model for end-stage liver disease (MELD) scores over the 24-week period. • Complications of CLD (frequency of ascitic paracentesis, number of hospital admissions, the incidence of serious infections such a spontaneous bacterial peritonitis). • For those who undergo LT, post-operative complications, e.g. length of admission. • Transplant free survival time. • Quality of life measures. • Physical activity indices.	• Change in clinical status. • Change in mucosal healing, as defined by Travis et al, [45], symptoms scoring including Harvey Bradshaw Index scoring and severity staging including Mayo scoring. • Complications of IBD (number of hospital admissions, number of acute flares). • Quality of Life measures. • Physical activity indices.	• Change in disease activity (ACR response criteria, DAS28 response, achievement of ACR/EULAR remission criteria). • Complications of RA (number of hospital admissions, number of acute flares) • Quality of life measures. • Physical activity indices.

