MRI femur	Axial and sagittal plane scans of each thigh will be obtained using an MR 3T scanner for higher quality, efficient imaging capture and 3D reconstruction. A T1 weighted Spin Echo protocol will be used (repetition time 600ms, echo time 15.2 ms, Field of view 512 × 512 mm, slice thickness 10mm, no gap between slices). Patients will lie supine on a preparation bed for up to 20 min to allow fluid shift stabilisation. A series of axial plane scans along the entire length of the quadriceps muscle group and sections at the L3 lumbar spine (L3 lumbar spine to quadriceps insertion on the tibia) will be collected. The contours of the quadriceps will be digitalised offline using the Osirix DICOM image analysis software (Pixmeo, Geneva, Switzerland) and the quadriceps muscle volume will be calculated [65]. 3-dimensional acquisition of both thighs and a Dixon sequence will be performed for fat analysis. Quadriceps muscle ACSA will be measured as described in the above. This midpoint of each femur length and the midpoint of VL (which is where ultrasound CSA measurements are taken from) will be marked with an external marker to ensure this is identified on MR images for analysis purposes and comparisons with ultrasound measurements. All image results will undergo a review by Consultant Musculoskeletal Radiologist.
Muscle biopsy	The patient will be fasted for ~6 h prior to the procedure. The ultrasound performed will identify the correct position to ensuring the sample is taken from the muscle belly. The non-dominant limb will be used if the dominant limb is not feasible. A small area of skin overlying the outer thigh will be cleaned with iodine solution. 5–10ml of 1% lignocaine is infiltrated into the subcutaneous adipose tissue and down to the muscle. After adequate anaesthetic, a small incision is made in the skin (approximately 5–7mm in length). A needle is inserted into the muscle and a small amount of muscle is taken using a well-described technique with a Bergstrom needle. A few passes may be performed. The incision will be closed using ‘steri-strips’ and a single suture, if required. A small dressing will then be placed over the biopsy site. Pressure and an ice compress will be applied to the area for 10 min by hand. A pressure bandage which will stay on for 8 h to decrease the risk of bruise formation. Patients will be asked to keep this area dry for at 3–5 days. All patients will receive after care advice and contact if any problems do arise.

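### The best non-invasive measures are to be identified by Spearman correlation alone, with no reference measure, no check for ultrasound-MRI bias and no interval for differences between measures

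*Protocol article*

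**What the plan says.** Under Experimental variables, the first primary item is "To identify the best non-invasive assessment parameters to evaluate sarcopenia in CLD, IBD and RA". The Statistical analysis plan gives one method for it: the assessment "will be made via analysis of the results of anthropometric, functional, and imaging data, using non-parametric analysis via Spearman correlation". The specific analyses listed after that are baseline description, correlation of sarcopenia measures with severity and quality of life, comparisons between diseases, and paired comparisons over six months. None of them evaluates one measure against another.

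Three other places bear on the point:
- Table 3 (MRI femur) says the scan sites "will be marked with an external marker to ensure this is identified on MR images for analysis purposes and comparisons with ultrasound measurements".
- Challenges in study design describes L3 lumbar muscle area, grip strength and SPPB as validated measures to set beside newer ones such as quadriceps ultrasound and dynamometry. It does not make any of them the reference for this question.
- Patient selection and sample justifies the group size by saying that "50 patients per disease group is sufficient for a Spearman correlation of ≥0.3 to reach statistical significance".

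The EWGSOP criteria appear in the Statistical analysis plan, but under the extent of sarcopenia ("compare these data with the EWGSOP criteria"), not under the choice of measure.

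**The concern.** To call a measure best, one needs something to judge it against and a criterion. Correlating anthropometric, functional and imaging variables with one another yields a matrix of coefficients, and the article does not say which row or column decides.

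Two consequences follow. First, ultrasound and MRI both give quadriceps cross-sectional area in the same units at matched sites. Whether ultrasound reads systematically high or low is then a natural question, and a rank correlation cannot answer it. Second, if measures are ordered by their observed coefficients, closely matched ones can change places by chance in a sample of 50. The group size was justified for testing one coefficient against zero, which is a different task.

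**Working it through.** **1. The plan's own figure.** Inputs from the article: n = 50 per disease, Spearman coefficient 0.3. Assumption: two-sided 5% level, because none is stated. The critical value is r = t/√(n − 2 + t²). With t = 2.011 on 48 degrees of freedom, r = 2.011/√(48 + 4.043) = 0.279. An observed 0.3 gives t = 0.3 × √(48/0.91) = 2.18, p = 0.034. The smallest n at which 0.3 is significant is 44. The statement is therefore arithmetically true.

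It concerns an observed coefficient against zero. By Fisher's z, power at a true 0.3 is Φ(0.3095 × √47 − 1.96) = Φ(0.16) = 56%, or 54% with variance 1.06/(n − 3).

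**2. Precision of one coefficient at n = 50.** The 95% interval is tanh(atanh r ± 1.96 × √[(1 + r²/2)/47]).
- Observed 0.7: 0.867 ± 0.319, giving 0.50 to 0.83.
- Observed 0.6: 0.693 ± 0.311, giving 0.37 to 0.76.

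The two overlap heavily. Both coefficients come from the same patients, however, so the difference has to be assessed directly.

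**3. Order of two measures against a common reference.** The article gives no expected correlations, so all sizes here are assumptions. Trivariate normal samples of 50 were simulated 20,000 times.
- 0.7 v 0.6, inter-measure 0.6: mean difference 0.099, SD 0.104, order reversed in 16% to 17%.
- 0.7 v 0.5, inter-measure 0.5: SD about 0.12, reversed in 4% to 5%.
- 0.7 v 0.4, inter-measure 0.5: reversed in under 1%.

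With inter-measure correlation varied from 0.4 to 0.7, and power taken from a test for two dependent correlations at the two-sided 5% level:

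| True gap | Pairs tried | Power | Order reversed |
|---|---|---|---|
| 0.1 | 0.6 v 0.5, 0.7 v 0.6, 0.8 v 0.7 | 13%–31% | 9%–23% |
| 0.2 | 0.7 v 0.5, 0.8 v 0.6 | 39%–74% | 1%–6% |
| 0.3 | 0.7 v 0.4, 0.6 v 0.3 | 56%–90% | at most 2% |

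With no true gap, at 0.7 v 0.7, the test rejected in 6% to 7% of runs, so these powers are slightly flattering. With six candidates, one at 0.7 and five at 0.6 (inter-measure 0.5), the true best ranks first in 55% of studies.

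**4. Agreement.** Suppose ultrasound area = 0.8 × MRI area in every patient. The ranks are identical, so Spearman is exactly 1 while every value is 20% low. With noise added, one simulated set of 50 (test = 0.7 × reference + noise, reference mean 60) gave a Spearman coefficient of 0.97, bias −18, limits of agreement −26 to −11 and a concordance coefficient of 0.36.

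Fifty pairs are enough to estimate limits of agreement usefully. The 95% half-width of each limit is about t × √(3/n) = 2.01 × √(3/50) = 0.49 standard deviations of the differences.

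**The case against.** The strongest reply is that this is an exploratory cohort, for which the authors say "therefore a sample size calculation was not applicable". It speaks of best parameters in the plural and sets no rule for choosing one. Its list of analyses is open-ended, the intention to compare ultrasound with MRI is stated, and a fuller plan may hold the details. That limits how far the point can go. It does not remove it, because the article itself ties this primary question to one method, and that method does not measure bias.

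Several stronger readings are tempting, and the documents do not support them:
- **That 50 patients cannot rank measures at all.** With assumed correlations of 0.7 and 0.5 the order is right in about 95% of studies, and with a gap of 0.3 in at least 98%.
- **That the plan could recommend a measure that misclassifies at any cut-off.** A constant 20% under-reading leaves discrimination intact once the cut-off is lowered by 20%. What is lost is interchangeability of values.
- **That grip strength would win by being correlated with itself.** This would need EWGSOP status to be the reference for this question. The plan attaches EWGSOP to the extent of sarcopenia.
- **That MRI is the declared reference standard.** It is not; the article only provides for the comparison.
- **That ranking by AUC would be better.** In the same simulations, with the reference dichotomised at assumed prevalences of 20% to 80%, AUC reversed the order in 23% to 27% of studies for 0.7 v 0.6 and 10% to 14% for 0.7 v 0.5. Both are worse than Spearman.

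**Conclusion.** The point holds in limited form. For a primary question, the article fixes Spearman correlation as the only method and names no reference measure. That method cannot show systematic bias between ultrasound and MRI area, whatever the sample size; this part rests on no assumption. The instability of the order is a matter of degree: material for gaps of about 0.1 (reversal in 9% to 23%), small at 0.2 (1% to 6%), negligible at 0.3. Those figures depend on the assumed correlations, normal data and all 50 patients in a disease group contributing each measurement. The group-size statement is not an error; it simply does not bear on comparing measures. This is an inexpensive improvement to the analysis, not a flaw that undermines the study.

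**What to change.** Amend the analysis wording as follows.

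1. State the reference measure for each domain. Examples are one of the measures that Challenges in study design calls validated, or MRI quadriceps area for ultrasound quadriceps area. A measure that serves as reference in a domain is not also a candidate there.
2. For ultrasound against MRI quadriceps area, report Bland-Altman bias with limits of agreement and a concordance coefficient, alongside Spearman. Confine this to pairs in the same units; it does not apply to grip strength, SPPB or dynamometry.
3. For candidates sharing a reference, report the difference between their Spearman coefficients with a bootstrap 95% interval, resampling whole patients so that the pairing is kept. Describe one as better only if the interval excludes zero.

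Sensitivity, specificity and AUC against EWGSOP status may be added as description, but should not decide the ranking.

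The cost is a little more analysis of data already planned, with no new visits or measurements. The downside is that the study may have to report that no measure is distinguishable as best. For a true gap of 0.1, about 80% power would need roughly 200 to 250 patients (0.8 v 0.7, inter-measure 0.6) or about 400 (0.7 v 0.6, inter-measure 0.5).

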**Methods:**

This prospective cohort study will consist of a multi-modal assessment of sarcopenia and its underlying mechanisms. Recruitment will target three chronic inflammatory diseases: chronic liver disease (CLD) (*n*=50), with a subset of NAFLD (*n*=20), inflammatory bowel disease (IBD) (*n*=50) and rheumatoid arthritis (RA) (*n*=50) both before and after therapeutic intervention. In addition, 20 age and sex matched healthy individuals will be recruited for comparison. Participants will undergo 4 assessment visits at weeks 0, 2, 12 and 24. Visits will consist of the following assessments: blood tests, anthropometrics, functional assessment, quadriceps muscle imaging, actigraphy, quality of life questionnaires, food diary collection and muscle biopsy of the vastus lateralis (at weeks 2 and 24 only). In addition, stool and urine samples will be collected for future microbiome and metabolomics analysis.

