## Methods

### Study overview

The proposed study is a single centre, longitudinal observational, prospective study of a cohort of patients with sarcopenia associated with chronic inflammatory disease, to identify generic and disease-specific mechanisms that potentially drive sarcopenia.

Patients recruited to the study will undergo several assessments (anthropometric, functional, serological, radiological, lifestyle and health-related quality of life evaluation) to assess their sarcopenia status and provide muscle biopsies on two occasions to allow further analyses including protein turnover, mitochondrial and satellite cell function, RNA sequencing, to be undertaken. Patients will be assessed at four defined time points: baseline, 2 weeks, 12 weeks and 24-week time points to allow analysis pre- and post-biologic therapy in the IBD and RA cohorts. Some of the CLD participants will undergo a liver transplant during their participation allowing a pre- and post-transplant comparison. Patients will be recruited from the University Hospitals Birmingham Foundation Trust, Birmingham, UK. Patients will continue with their standard of care management as determined by their regular specialty team. Age and sex matched healthy controls will undergo the same assessments and provide a muscle biopsy at a single study visit. They will comprise of people without sarcopenia or any significant comorbidities, with a regular level of activity (ie those without a high level of exercise/performance or not sedentary).

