**Healthy controls**	1. Adults aged ≥ 18 years. 2. Able to confirm written consent to the study. 3. No co-existing chronic inflammatory condition, cancer or significant premorbid disease pathology. 4. No suspicion or evidence of sarcopenia. 5. No previous transplantation.	1. Refusal or lack capacity to give informed consent. 2. Pregnancy. 3. Any recent acute illness or surgery requiring significant treatment or hospitalisation (within the last 12 weeks). 4. Any systemic corticosteroid use or replacement. 5. For muscle biopsies only: a. Obvious injury to both thighs. b. Active bleeding of site, pre-procedure. c. Abnormal observation parameters. d. Acute illness. e. INR > 1.6. f. Platelet count < 30. g. Anticoagulation which cannot be paused due to increased risk to pre-existing comorbidity.

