##### Control cohort

Poster advertising recruitment will be disseminated across the University of Birmingham, targeting staff and students. All participants who volunteer will then be screened for eligibility.

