### Confounding medications

Most patients with inflammatory disease are treated with a variety of medications. For the purposes of this study, we have allowed those on oral steroids or DMARDs in all cohorts. Additionally, those within the CLD cohort may have their follow up visits post liver transplantation, for which they will be treated with immunosuppression. Given it is unsafe to pause any of these, and this is an observational study, we are recording these data. We recognise it may compound muscle loss.

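### Between-disease comparisons of muscle measures use unpaired rank-type tests with no adjustment for age, sex or body size, and no described step balances the groups on these

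*Protocol article*

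**What the plan says.** The section Statistical analysis plan of the protocol article lists the specific analyses. For contrasts between cohorts it commits to one method: "Comparisons between disease types will be made using non-paired, non-parametric testing". No covariate, stratification or regression model for age, sex or body size appears anywhere in the article. The section names no test for patients against healthy controls.

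On the controls, Patient selection and sample says "We will also recruit an age-sex matched sample of twenty healthy individuals as a control cohort for comparison". The abstract and Study overview repeat the claim: "Age and sex matched healthy controls will undergo the same assessments and provide a muscle biopsy at a single study visit". The recruitment text under Control cohort reads "Poster advertising recruitment will be disseminated across the University of Birmingham, targeting staff and students", followed by "All participants who volunteer will then be screened for eligibility". The healthy-control criteria in Table 1 ask for age 18 or over and contain no age band, sex quota or matching rule.

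On steroids, Table 1 excludes controls for "Any systemic corticosteroid use or replacement". For patients, Confounding medications says "we have allowed those on oral steroids or DMARDs in all cohorts", adds that these data are recorded, and recognises that such treatment may affect muscle loss.

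**The concern.** Grip strength, knee-extension torque and muscle area or volume vary with sex, age and body size whatever the disease. The patient groups come from a liver transplant assessment clinic, a NAFLD clinic, an IBD biologic clinic and an RA biologics registry. The only age criterion is 18 or over, so nothing in the design makes these groups alike in age or sex. An unpaired two-group test compares the whole distributions and credits any demographic difference to the disease.

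The study's stated purpose is to separate generic from disease-specific mechanisms, so the between-disease contrast carries weight. A demographic difference could be reported as a difference in sarcopenia or in its mechanism. The control group might have served as a common demographic reference, but the article does not say how, or to which cohort, it is matched. The differing steroid rules raise the same kind of problem for the serum cortisol, cortisone, DHEA and DHEA-S comparisons with controls.

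**Working it through.** **1. The plan's own figure.** The only numerical justification is that 50 patients per disease make a Spearman correlation of 0.3 or more significant. The critical value is r = t/√(n − 2 + t²). With n = 50 and a two-sided 5% level (assumed, as the article gives none), r = 0.279, and r = 0.30 gives p = 0.034. The figure reproduces, but it concerns correlations within a cohort and has no bearing on the group contrasts.

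**2. Inputs for the group contrast.** From the article: 50 patients per disease group and an unpaired non-parametric test. Assumed, because the article gives no age or sex distribution: sex gap in grip D = 10 or 15 kg, within-sex SD 7 kg, shares of women p₁ and p₂, and no true disease effect.

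**3. Approximation by hand.**
- Spurious mean difference: Δ = D × (p₂ − p₁)
- Variance in each group: v = 7² + p(1 − p)D²
- Standard error: SE = √((v₁ + v₂)/50)
- Rejection rate: P(Z > 1.96 − Δ/SE) + P(Z < −1.96 − Δ/SE)

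For 45% v 65% women and D = 10: Δ = 10 × 0.20 = 2.0 kg; v₁ = 49 + 24.75 = 73.75; v₂ = 49 + 22.75 = 71.75; SE = √(145.5/50) = 1.706; Δ/SE = 1.172; rejection rate 0.216.

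For D = 15: Δ = 3.0 kg; v₁ = 104.69; v₂ = 100.19; SE = √(204.88/50) = 2.024; Δ/SE = 1.482; rejection rate 0.317.

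| Women, group 1 v 2 | Approximation, D = 10 / 15 kg | Simulated Mann-Whitney, range over runs and both gaps |
|---|---|---|
| 50% v 50% | 5% / 5% | about 5% |
| 50% v 55% | 6% / 7% | 5-7% |
| 50% v 60% | 9% / 11% | 9-12% |
| 45% v 65% | 22% / 32% | 21-32% |
| 40% v 70% | 43% / 62% | 41-63% |

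Simulated regressions that adjust for the imbalanced factors stay at about 5% throughout.

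**4. A second set of assumptions.** Here the measure falls by 0.3 residual SD per SD of age and the sex difference is 1.0 residual SD, with 50 v 50 and 4,000 runs per cell. The unadjusted test rejects in 5% of runs when the groups are balanced. It rejects in 10% with an age gap of 0.5 SD, 23% with 1 SD, 25% with a 30-point sex gap, and 50% with the 0.5 SD age gap and the sex gap together. A linear model with age and sex stays between 4.6% and 5.3% in every cell.

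**5. Controls, by comparing the text.** Three places declare age and sex matching. The recruitment paragraph and the Table 1 criteria give only a source of volunteers and a screen for eligibility. Neither names a cohort to be matched. One set of 20 can match CLD, NAFLD, IBD and RA together only if those cohorts have similar age and sex distributions, and the article does not say whether they do.

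**The case against.** **A reader might infer that university volunteers cannot match these cohorts.** The documents do not support that. They give no ages or sex mix for any group, staff may span working ages, and volunteers could be selected to fit. A condensed article may also leave the matching procedure to the full protocol. What stands is narrower: the matching is declared, but its method and target are not described.

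**A reader might also take the quoted sentence to fix an unadjusted test against controls.** It covers disease types only. No test is named for controls, so no false-positive figure for that contrast can be pinned on the plan.

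**Steroid use is not overlooked.** Confounding medications acknowledges it and says it is recorded. That passage does not discuss the hormone assays, so a sensitivity analysis is still worth adding, but a charge that the authors ignored steroids would be wrong.

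**The primary aims are partly protected.** Six-month change is tested within person, so fixed sex differences cancel, and the extent of sarcopenia is set against EWGSOP criteria within each disease. This lowers the severity. It leaves the cross-disease contrast exposed.

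**The article warns that comparison between groups is limited.** The reason it gives is differing standards of care, not age or sex.

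**A fuller analysis plan might add adjustment.** It might, but the published text commits to a test that does not adjust, and that commitment would then need correcting.

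**Conclusion.** The concern holds for the between-disease comparisons. As written, the plan can report a demographic difference as a disease difference. The size depends wholly on how unlike the cohorts are, which the article does not show. Under the assumed sex gap and SD, the effect is slight for a 5-10 point difference in the share of women (about 5-12% false positives), material at 20 points (21-32%) and severe at 30 points (41-63%). These are rates conditional on assumed imbalances, not estimates for this study. For the controls, the finding is a matching claim without a described method or target, not proof of a mismatch. Severity: should be fixed. The data are unaffected and the remedy lies in the analysis.

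**What to change.** 1. Make the main between-disease analysis of each muscle measure a regression on group with age, sex and, for mass measures, height. Use a linear model, or an ordinal or rank-based one for skewed measures. The unadjusted test can stay as a descriptive companion.
2. Name the same model for patient-control contrasts, where the article names no test.
3. Rely on that model rather than on the matching label. Keep the description as age and sex matched only if the matching was done, and then state the target cohort and the method. Enrolment was due to finish in July 2021, so the remedy should not depend on new control recruitment.
4. Add a sensitivity analysis of cortisol, cortisone, DHEA and DHEA-S restricted to patients not on systemic steroids, using the medication data already recorded.

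Age and height are listed assessments, sex is needed for the declared matching, and concomitant medications are in the case report form. The cost is a few degrees of freedom per model and a little more analysis work.
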